### Sample size

Sample size calculation was performed a priori according to the primary outcome on an intention-to-treat basis. A total of 72 nurses (36 nurses per treatment condition) achieves 80% power to reject the null hypothesis of equal means when the population mean difference is − 1.21 with a standard deviation for both groups of 1.8 and a significance level of 0.05 using a two-sided two-sample equal-variance *t*-test (PASS 2021). Both the expected mean change and the standard deviation were found by exploring data (which are available from the authors) regarding the distress of nurses working in COVID-19 wards [1, 4].

### Recruitment

The study description and the invitation to participate will be published in the hospital’s newsletter and will be emailed to the nurses’ address by the Verona Hospital Trust Administration. If the study does not obtain enough responses from the newsletter advert, the research group will organize in-person meetings with all nursing staff working within the selected hospital units to present the study, to explain its rationale and to ask their availability to participate. This may allow to increase the number of potential participants. All nurses who express an interest in participating will receive (via e-mail) an information sheet containing all the project details together with a link to the online screening questionnaire. They will find the participant consent form and the consent form for the use and processing of personal data on the same page. The screening questionnaire will allow us to assess whether the participant meets the inclusion criteria. If they do, they will be added to a temporary list of candidates; if they do not, they will be excluded from the trial. However, those participants not meeting inclusion criteria but requiring psychological support will may seek specialized mental healthcare through the Psychiatric Consultation Liaison Service based at the Psychosomatics Unit within the Verona Academic Hospital Trust.

### Assignment of interventions: allocation

Participants will be randomly allocated to the intervention or the WL control group with an allocation ratio of 1:1. Participants allocated to the experimental group will receive the intervention immediately after randomization, and those assigned to the control group will be offered the same intervention 6 months after. The experimental intervention will take place over 6-weeks. The pre-test, post-test, and 1-month follow-up will be carried out at the same time for both study groups.

The trial statistician will prepare the sequence of treatments randomly permuted into blocks of 2. The randomization schedule will be generated with Stata software (version 17.0; Stata Corp, Corp, College Station, TX, USA) using the ‘ralloc’ command for random allocation of treatments balanced in blocks. The Emotional Exhaustion sub-scale (EX) score of the MBI-GS assessed at the screening phase will be used to perform a stratified randomization based on the median value (EX ≥ median vs. EX< median). Two lists of randomizations will be generated according to the levels of the stratification variable. The trial statistician will communicate by email the randomization results to the responsible for trial, who will notify to the participants by email if they belong to the intervention or the WL control group.

The trial will begin in September 2022. Enrolment will end as soon as the expected number is reached (36 for the intervention group and 36 for the control group). Before the intervention, participants randomly assigned to the intervention group will be divided into three subgroups consisting of 12 individuals. Each subgroup will follow the mindfulness courses (led by the same instructor) for 6 weeks. The courses will be delivered every Monday for subgroup 1, Tuesday for subgroup 2, and Wednesday for subgroup 3. Nurses will attend the intervention during working hours as part of the continuing professional education (CPE) courses provided by the Verona Hospital Trust Administration.

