### Statistical methods

Statistical analysis will be based on an intention-to-treat (ITT) basis, comparing outcomes from all nurses allocated to the two trial arms. Findings will be reported according to the CONSORT guidelines for parallel-group randomized trials [47].

Personal socio-demographic information and job-related characteristics will be summarized descriptively according to the treatment arms. Categorical data will be presented as frequencies and percentages. Means, standard deviations, medians, interquartile ranges, and minima and maxima will be presented for continuous data. To verify the success of randomization, the baseline characteristics of the two treatment groups will be compared: continuous variables will be compared with a *t*-test (for normally distributed variables) or the Mann-Whitney *U* test (for non-normally distributed variables). Categorical variables will be evaluated with the chi-square or 2-tailed Fisher exact test. Change scores will be calculated. Data will be presented as percentages for categorical data and means and standard deviations for continuous data; 95% CIs will be used to indicate uncertainty around the estimates.

Follow-up data will be analysed using mixed models to establish the correlation between repeated measurements and examine main effects and their interaction, adjusting for the baseline score. The presence of multi-collinearity, interaction, and higher power terms will be assessed to check final model validity. Statistical significance will be defined at two-sided *p* < .05. All analyses will be carried out using Stata 17.0 for Windows.

The effects of baseline covariates expected to have an important influence on the primary outcome will be controlled for by comparing covariate-adjusted analyses with unadjusted analyses. Certain covariates that will be considered at baseline will refer to demographic variables (e.g. gender, age, and education level), the organizational context, and participation in non-mindfulness support courses.

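### The 80% power makes no allowance for treating the intervention arm in three course groups of 12; it holds only if outcomes within a course are uncorrelated

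*Protocol article*

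**What the plan says.** Under Assignment of interventions: allocation, nurses are randomised individually "with an allocation ratio of 1:1". Before treatment starts, "participants randomly assigned to the intervention group will be divided into three subgroups consisting of 12 individuals". Each subgroup has a fixed weekday for six weeks, and one instructor teaches all three. The Interventions section makes discussion within the group, and feedback on shared experience, part of the programme. Under Trial design the comparator is a waiting list, which has no groups during the assessed period.

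The Sample size section states: "A total of 72 nurses (36 nurses per treatment condition) achieves 80% power to reject the null hypothesis of equal means". Its inputs are a difference of -1.21 and a common SD of 1.8, tested at the two-sided 5% level by a t-test for two independent samples with equal variances. It uses no design effect and no ICC.

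Statistical methods states: "Follow-up data will be analysed using mixed models to establish the correlation between repeated measurements", with adjustment for the baseline score. The covariates it lists concern demographics, organisational context and other support courses. Course group is not among them, and the article nowhere mentions clustering.

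**The concern.** This is a partially nested design: the intervention arm is grouped after randomisation and the control arm is not. Nurses who sit in the same group for six weeks share its dynamics, its session day and one another's accounts. Their outcomes may therefore resemble each other more than those of nurses in different courses. If so, the mean of the intervention arm is less precise than 36 independent observations would make it.

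Two things are then at stake. The trial would have less power than stated. An analysis that ignores course would also give an interval that is too narrow, and in a superiority trial that favours declaring the programme effective.

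**Working it through.** **Inputs from the Sample size section:** 36 nurses per arm, difference 1.21 in absolute value, SD 1.8 in both arms, two-sided 5%, equal-variance t-test. **Input from the allocation section:** three courses of m = 12. **Assumed, because the article gives no value:** ICC of 0 to 0.10 in the intervention arm, total SD held at 1.8.

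**Step 1: reproduce the stated power.** SE = 1.8 × √(2/36) = 0.424. Noncentrality = 1.21/0.424 = 2.85. On 70 df, power is 80.3%. With 35 per arm it is 79.2%. So 36 per arm is the smallest number that reaches 80% under independence, and nothing is held in reserve.

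**Step 2: allow for clustering in the intervention arm only.** Design effect DE = 1 + (12 − 1) × ICC for that arm and 1 for the waiting list. SE = 1.8 × √((DE + 1)/36). Example at ICC 0.05: DE = 1.55, SE = 1.8 × √(2.55/36) = 0.479, noncentrality = 1.21/0.479 = 2.53, power 70.2%.

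| Assumed ICC | DE | SE relative to independence | Power (70 df) | Type I error of unadjusted t-test |
|---|---|---|---|---|
| 0 | 1.00 | 1.000 | 80.3% | about 5.0% |
| 0.01 | 1.11 | 1.027 | 78.2% | about 5.6% |
| 0.02 | 1.22 | 1.054 | 76.1% | about 6.3% |
| 0.05 | 1.55 | 1.129 | 70.2% | about 8.3% |
| 0.10 | 2.10 | 1.245 | 61.8% | about 11.5% |

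The third column is √((DE + 1)/2). An interval that ignores course is too narrow by about that factor.

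**Step 3: type I error.** The last column is simulated: three course effects with variance ICC × 1.8², 12 nurses per course, 36 independent controls, and a mean course effect of zero. Repeated runs gave 8.2 to 8.5% at ICC 0.05 and 11.5 to 11.9% at ICC 0.10. An approximation agrees. At ICC 0.05 the unadjusted test expects an intervention-arm variance of 1.8² × (1 − 11 × 0.05/35), so the ratio of true to reported SE is about 1.134, and 2 × (1 − Φ(1.96/1.134)) = 8.4%.

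**Step 4: can three courses estimate the course variance?** The usual estimate is zero or below whenever the between-course mean square is less than the within-course one. With 2 and 33 df and λ = (1 + 11 × ICC)/(1 − ICC), this has probability 1 − (1 + 2/(33λ))^(−16.5). At ICC 0.02, 0.05 and 0.10, λ = 1.245, 1.632 and 2.333, and the probability is about 54, 45 and 34%. If Satterthwaite degrees of freedom are used instead (2 df for the intervention mean), power at those ICCs is about 63, 54 and 43%.

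**The case against.** **The size is unknown.** The article gives no ICC. All courses share one instructor, one site and one programme, so differences between instructors cannot add to the variation between courses. What remains is group interaction, session day and how nurses are sorted into groups. This stands. Values near zero belong in the range; at 0.01 the loss is about two points of power, and at 0 there is none.

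**The analysis plan is not shown.** A reader might infer that the mixed model excludes a course term. The article does not say so: it names one source of correlation and leaves the random-effects structure open, and an analysis plan could add course. This also stands. It does not rescue the power statement, which is fixed in the article and which a course term could only lower.

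**The type I figures need a particular null.** They apply when courses truly differ but average to no effect. If the programme changes nobody's outcome, individual randomisation keeps the error at its nominal level however one arm is later divided. The figures must carry that condition.

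**Baseline adjustment may recover power.** If 1.8 is the SD of a raw score, which the article does not make clear, then at ICC 0.05 power would be about 73, 79 or 89% for assumed baseline correlations of 0.3, 0.5 or 0.7. At ICC 0.02 it would be about 80, 86 or 95%. The article gives no correlation and its 80% takes no credit for one, so this gain can be neither claimed nor ruled out. It would not remove correlation that arises within courses.

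**Conclusion.** The point holds in conditional form. The 80% is correct arithmetic for 72 independent nurses, at the smallest sample that reaches it, in a design that gives a reason to doubt independence in one arm. For any positive ICC within courses, the power under the stated assumptions is lower and an interval that ignores course is too narrow. Over assumed ICCs of 0.01 to 0.10, power is about 78 to 62%. This takes the total SD as 1.8, 70 df and no baseline adjustment.

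A reader might go further and infer that the trial is underpowered, or that its error rate is above 5%, as established facts. The article does not support that. Both depend on an ICC it does not give, and the second also on courses that truly differ around a zero average.

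**What to change.** 1. In the Sample size section, restate the power over ICC 0 to 0.10 in the intervention arm and say that 80% holds only at ICC 0.
2. Record course membership with each intervention nurse's data. Data collection and management describes an anonymous survey linked by self-generated passwords, so if course is not captured with the responses it may not be recoverable later.
3. Pre-state a sensitivity analysis that gives the primary treatment interval with the intervention-arm variance multiplied by 1 + 11 × ICC at fixed assumed values, for example 0.02, 0.05 and 0.10.
4. A random course effect in the intervention arm only, with small-sample degrees of freedom, may be reported as supportive. It should not be the sole remedy. With three courses its variance will often be estimated at zero, which returns the independent result; otherwise it leaves few degrees of freedom.

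The cost is one extra data field, a few lines of analysis code, a less favourable stated power and wider sensitivity intervals. With the SD as planned, the intervals would be about 1.05, 1.13 and 1.245 times as wide at the three ICCs. No extra nurses and no change to the programme are needed.

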### Assignment of interventions: blinding

Participants will be screened by an independent psychologist after completing the MBI-GS. The randomization will be independently conducted by the trial statistician. The assessments pre-treatment, post-treatment, and at 1-month post-treatment will be completed online. The participants and the treatment psychologist will not be blind.

### Data collection and management

All research data will be retained in the psychiatry section of the University of Verona. Participants scoring above the cut-off score of the screening questionnaire will enter the study and will complete the assessments through a web-based system. Online questionnaire completion time is estimated at approximately 30 min and will be easily carried out using a PC, tablet, or smartphone. The battery of questionnaires will be compiled using the online system Lime Survey (www.limesurvey.com). Data will be stored on the cloud and passwords protected. At the baseline evaluation, each participant will be required to generate a password that should have been used also at the subsequent follow-ups; this was required for the research team to longitudinally link the questionnaires completed by a given nurse at each evaluation point. The study description and the invitation to participate as well as the link to the online questionnaire will be sent via e-mail to all nurses who meet the criteria by the trust administration. A reminder for completing the questionnaire was sent around after one week. The survey will be anonymous, and confidentiality of information will be guaranteed. The data collected will be downloaded and managed by the person responsible for data management and statistical analysis ([name]). [name] will be responsible for data retention. In accordance with the Declaration of Helsinki, participant confidentiality will be fully preserved throughout the study. It will not be possible to associate the results with the single compiler of the questionnaires or with the single structure to which they refer in any published papers.

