If participants of either group report any adverse events during the trial, this will be registered in the electronic database system. Serious adverse events will be reported to the ethics committee. If participants require additional mental health support, they will be referred to the regular services, but it is also possible for participants to consult with an appointed psychologist if they so request or if the trainer so advises.

Each session will focus on topics that will be explored through specific exercises, presented by a licensed psychologists with demonstrated experience in the application of mindfulness-based protocols and who meets the criteria of the internationally agreed good practice guidelines of the UK network for mindfulness-based teachers.

If a given participant at the end of the trial continues to display high or higher levels of distress, they will be referred to the Psychiatric Consultation Service at the UOC of Psychosomatics, Verona Hospital Trust. This service has provided an individual help pathway for HCWs with psychological distress since the beginning of the pandemic. The WL is the control group planned for this study. It will remain in place for the entire period of the intervention. Details on the rationale of the study are shown in the flowchart (Fig. 1).

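### The anonymous survey, linked by a password each nurse invents after randomisation, does not as described supply the arm the analysis needs and conflicts with referring individual participants

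*Protocol article*

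**What the plan says.** Under Data collection and management, the protocol article says "The survey will be anonymous, and confidentiality of information will be guaranteed". It names one device for joining a nurse's questionnaires: "each participant will be required to generate a password that should have been used also at the subsequent follow-ups". It gives the reason: "this was required for the research team to longitudinally link the questionnaires completed by a given nurse at each evaluation point". No other key is described.

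The allocation section works on identified people. The screening emotional exhaustion (EX) score "assessed at the screening phase will be used to perform a stratified randomization based on the median value", and the trial statistician sends the result to the person responsible for the trial, "who will notify to the participants by email if they belong to the intervention or the WL control group". Table 2 places randomisation at T0 and the first outcome questionnaires at T1.

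Statistical methods plans an intention-to-treat analysis, "comparing outcomes from all nurses allocated to the two trial arms", using mixed models adjusted for the baseline score. The primary outcome is change in EX from pre-treatment to 1 month after treatment.

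The Interventions section adds: "If a given participant at the end of the trial continues to display high or higher levels of distress, they will be referred" to a psychiatric consultation service. Oversight and monitoring says that participants harmed by the intervention, and waiting-list nurses whose mental health worsens, will be referred and excluded from the study.

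**The concern.** Two sets of records need to meet. Screening EX, stratum and arm belong to a named nurse with an e-mail address. The T1, T2 and T3 outcomes belong to a password that the nurse made up. The described procedure joins the outcome records to each other, but contains no step that joins them to the allocation list.

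Three things are at stake. First, every outcome record needs a randomised arm before any between-arm comparison can be made. Second, a T3 record whose password does not match has no baseline, and the primary outcome is a change from baseline. That loss can occur even when every nurse completes every questionnaire. Third, the protocol commits to acting on the distress of individual participants, while saying that the instrument which measures distress on schedule is anonymous.

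**Working it through.** **Setting the statements side by side**

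| Step | Record held by | Section |
|---|---|---|
| Screening EX, used for the stratum | Identity | Recruitment; allocation |
| Allocation at T0, notified by e-mail | Identity | Allocation; Table 2 |
| Outcomes at T1, T2, T3 | Self-made password, survey anonymous | Data collection and management |
| Comparison by allocated arm, adjusted for baseline | Needs arm and T1–T3 together | Statistical methods |
| Referral, or referral and exclusion, of a distressed participant | Needs identity | Interventions; Oversight and monitoring |

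The password is created at the baseline evaluation, which Table 2 calls T1. The allocation list is made at T0, so the password does not yet exist and cannot be on the list when it is drawn up. No later step attaches it. The third row therefore does not feed the fourth or the fifth through anything the article describes.

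**Reproducing the plan's power**

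Inputs from the Sample size section: difference 1.21 in absolute value, SD 1.8, 36 per arm, two-sided alpha 0.05, equal-variance t-test.

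Noncentrality = 1.21 / (1.8 × √(2/36)) = 1.21 / 0.4243 = 2.85, with 70 degrees of freedom. Power from the noncentral t is 0.803, so the stated 80% reproduces. With 35 per arm it is 0.792, so the sample size leaves no margin for lost records.

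**Illustrating unmatched records**

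The documents give no failure rate. Assume a fraction f of nurses in each arm lose their primary change score because the password does not match. Then n per arm = 36 × (1 − f), with the same formula:

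| Assumed f | Nurses lost of 72 | n per arm | Noncentrality | Power |
|---|---|---|---|---|
| 0 | 0 | 36 | 2.85 | 0.803 |
| 5% | 3.6 | 34.2 | 2.78 | 0.782 |
| 10% | 7.2 | 32.4 | 2.71 | 0.759 |
| 15% | 10.8 | 30.6 | 2.63 | 0.735 |

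This is a complete-case t-test. It measures only password mismatch between assessments and assumes that arm is known for the records that do match. It does not measure the consequence of having no link to arm.

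**The case against.** The strongest reply is that anonymous is a loosely used word here and the working data are in fact pseudonymous. The same section ends by limiting non-identifiability to results linked with a single respondent "or with the single structure to which they refer in any published papers", a limit that strict anonymity would make unnecessary. Data Availability offers an anonymous copy of the file, which suggests that the working file is something else. The analysis plan summarises characteristics by arm, so the investigators evidently expect to know it. This is also a journal article, and a key file or arm-specific survey links could be set out in a full protocol that is not shown.

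Much of this stands, and it rules out stronger readings. A reader might infer that records cannot be tied to follow-up at all. They can, because the password is there for that purpose; it is fallible, not absent. A reader might infer that arm and screening score can never be attached. The article shows only that the mechanism it describes does not do so. A reader might also infer that referral on distress is impossible. The Interventions section names no questionnaire or cut-off as the trigger, and it offers consultation at the participant's request or on the trainer's advice.

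The planned analysis softens the power figures as well. A mixed model keeps nurses with incomplete follow-up, so a nurse with an unmatched T3 could still contribute linked T1 and T2 data.

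The loose-wording reading does not remove the point, however. If the data are linkable, the article and any consent text that repeats it describe them wrongly. If they are not, the arm is missing. Mixed models and multiple imputation cannot restore a link between an orphaned record and its arm or baseline. Waiting-list nurses have no trainer during the trial, so the trainer route does not cover them.

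**Conclusion.** The concern holds in a limited form. The article states a linkage mechanism that, as written, does not connect outcome records to the screening and allocation records needed for analysis by arm. The mechanism is open to password error, and it conflicts with the statements on referring or excluding individual participants. No figure in the protocol is wrong.

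The size is not known from the documents. Under an assumed 5% to 15% of unmatched records, complete-case power would move from 0.803 to between 0.782 and 0.735, the same as ordinary attrition of that extent. The conclusion rests on the text and would stand without these figures. It should be settled before data collection, because records gathered without a link to arm may not be repairable afterwards.

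**What to change.** 1. Replace the self-chosen password with a study ID issued at consent or screening. Record it on the randomisation list and embed it in each nurse's individual T1, T2 and T3 survey link. Keep the key between ID and name separately, for example with the data manager.
2. In the protocol and consent text, describe the data as pseudonymised and confidential instead of anonymous.
3. Reconcile Data collection and management with the referral statement under Interventions and the referral and exclusion statement under Oversight and monitoring, so that all three agree on whether an individual's responses can be identified during the trial. How distress is to be managed is for the investigators to decide.

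The cost is survey set-up and revised consent and privacy wording. The one real downside is that some nurses may answer slightly less candidly than under full anonymity, particularly as the survey link is sent by their employer's administration.
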